# German adaptation of the Resources for Enhancing Alzheimer’s Caregiver Health II: study protocol of a single-centred, randomised controlled trial

**DOI:** 10.1186/1471-2318-14-21

**Published:** 2014-02-12

**Keywords:** Dementia, REACH II, Intervention, Informal caregivers

## Abstract

**Background:**

Caring for a family member with dementia is extremely stressful, and contributes to psychiatric and physical illness among caregivers. Therefore, a comprehensive programme called Resources for Enhancing Alzheimer’s Caregiver Health II (REACH II) was developed in the United States to enhance the health of Alzheimer’s caregivers. REACH II causes a clear reduction of the stress and burdens faced by informal caregivers at home. The aim of this protocol is to adapt, apply, and evaluate this proven intervention programme in a German-speaking area for the first time. This newly adapted intervention is called Deutsche Adaption der Resources for Enhancing Alzheimer’s Caregiver Health (DeREACH).

**Methods:**

A total of 138 informal caregivers at home are recruited in a single-centred, randomised controlled trial. The intervention (DeREACH) consists of nine home visits and three telephone contacts over six months, all of which focus on safety, psychological well-being and self-care, social support, problem behaviour and preventive health-related behaviours. A complex intervention assessment on effectiveness will be adopted when the primary outcome – namely, the reduction of caregiver burden – and other secondary outcomes, including changes with regard to anxiety and depression, somatisation, health-related quality of life, and perceived social support, are measured at baseline, as well as immediately and three months after the intervention. The change from baseline to post-intervention assessment with regard to the primary outcome will be compared between treatment and control group using t-tests for independent samples.

**Discussion:**

It is anticipated that this study will show that DeREACH effectively reduces caregiver burden and therefore works under the conditions of a local German health-care system. If successful, this programme will provide an effective intervention programme in the German-speaking area to identify and develop the personal capabilities of informal caregivers to cope with the burdens of caring for people with dementia.

**Trial registration:**

NCT01690117

## Background

Caring for people with dementia is connected with enormous personal responsibilities and restrictions; therefore, family caregivers of people with dementia often feel more burdened and stressed than caregivers of older people with physical impairments [1]. Due to this high stress level, there is a higher risk of these informal caregivers becoming physically or mentally diseased [2]. For these caregivers, the conditions of experiencing stress and burden are complex [3], and the non-cognitive symptoms of dementia such as psychotic symptoms, depression, and challenging behaviour seem to play a significant role in this process [4].

American scientists created a wide-ranging programme regarding the development of effective interventions to support informal caregivers of people with dementia. In this programme, known as Resources for Enhancing Alzheimer’s Caregiver Health (REACH I) [5,6], the researchers tested, evaluated, and compared various single- and multi-component interventions. Based on these findings, Resources for Enhancing Alzheimer’s Caregiver Health II (REACH II), an intensive and individualised intervention with multiple components, was generated. REACH II causes a clear reduction of the stress and burdens faced by care-giving family members [6]. Nevertheless, despite its advantages and proven effectiveness, it has not been applied to German-speaking areas.

Hence, the planned study aims at the adaptation of the American REACH II intervention to the conditions of the German health-care system in the Deutsche Adaption der Resources for Enhancing Alzheimer’s Caregiver Health (DeREACH), as well as the evaluation of the DeREACH intervention (the official agreement of the developers of REACH II with this intention is on hand).

We assume that the DeREACH intervention as opposed to the standard supply of health-care services will reduce the burden of informal caregivers. Furthermore, positive effects on depression and somatisation as well as health-related quality of life and social support for care-giving family members can be expected.

## Methods

### Study design

The study has been designed as a non-blinded, randomised, and controlled trial. The intervention group receives the DeREACH intervention and the control group receives the standard supply of health-care services; both groups receive baseline, final, and follow-up assessments.

The design, conduct, and reporting of the DeREACH study will adhere to the Consolidation Standards of Reporting Trials (CONSORT) guidelines [7].

### Inclusion and exclusion criteria

We only include informal caregivers of people with dementia who live at home with their relatives and are residents of Leipzig. In addition, participants must be able to speak German fluently and a diagnosis of dementia should have been established by a physician for each care recipient.

### Recruitment of participants

The recruitment process is supported by the Geriatric and Gerontopsychiatric Network of Leipzig. This network was established to advance the collaboration of various health-care systems and to assure that people with dementia in particular receive constant attention. It involves memory clinics, home-care agencies, nursing homes, voluntary helpers, associations, and day-care facilitates. These participating facilities suggest eligible subjects, inviting them to attend the study. Furthermore, we address potential participants via articles and announcements in newspapers and via posters and flyers that are available in several health-care facilities.

### Randomisation

The participants are split into the study groups randomly. To obtain the same number of subjects in the intervention and the control group, we use a randomisation in blocks [8]. Moreover, we use a central randomisation via randomisation lists realised by an online procedure of the Medical Faculty of the Ludwig-Maximilians-University of Munich [9]. The outcome rater is not informed about the randomisation code of a participant before opening a sealed envelope with the code inside after completion of the baseline assessment.

### Blinding

The informal caregivers, their relatives with dementia, and the study staff cannot be blinded in matters related to the study group.

### Study procedure

A nurse from University Hospital Leipzig makes contact with our participants and arranges the first appointment. One or two outcome raters visit informal caregivers at home to conduct the baseline assessment. In addition, we undertake a dementia screening for diagnosing the degree of cognitive impairment [10]. This takes place during the first appointment at home with the diseased individual to confirm the diagnosis of dementia.

After completion of the baseline assessment, an envelope containing the subject’s randomisation code is opened to allocate the participant to the intervention group or control group.

Study staff will make another appointment for the first home visit with the informal caregivers allocated to the intervention group. Altogether, the informal caregivers in the intervention group receive nine home visits and three phone sessions. Every home visit is structured in its sequence and appointments will be scheduled visit by visit. Usually, the whole intervention lasts six months and a post-intervention assessment takes place immediately after completion. A follow-up assessment takes place nine months after the baseline assessment.

The informal caregivers of the control group only receive the standard supply of health care services and the assessments outlined above. An overview of the study design and the assessment points is provided in Figure 1.

**Figure 1 F1:**
[figure not shown]
Study design.

The intervention is executed by medical staff (for instance, nurses and occupational therapists). Prior to the intervention, these interventionists obtain training and a manual related to the intervention. Furthermore, they are attended and supported by research staff.

### Intervention

For this trial, the original REACH II intervention will be translated into the German language. Regional distinctions have to be adapted to meet conditions in Germany. Especially with regard to the areas of social support and self-care, it was necessary to include regional facilities and other offers of support. All 12 sessions of the DeREACH intervention are described in a study manual. Departing from the original REACH II intervention, we will train medical staff and not volunteers to perform the intervention. Another feature that required modification was the computer telephone integration system that the REACH II intervention provided to all participants, because the requirements are not available in the study area.

DeREACH is a multi-component intervention involving various strategies and techniques, such as psychoeducational information, problem-solving tasks, risk management, role playing, stress management, and social support. Five potential areas of risk in care giving receive particular attention in the intervention: safety, emotional well-being and self-care, social support, problem behaviour and preventive health behaviour. The intervention occurs over six months and includes 12 individual sessions (nine at home and three by telephone). Table 1 outlines a typical home session. A detailed description of the original REACH II intervention is available at the Epidemiology Data Center of the University of Pittsburgh [11].

**Table 1 T1:** Exemplary structure of an intervention session

**Prior to a session, the interventionist reviews the risk worksheet**		
1)	Brief explanation of the focus of the session and how it will be structured	
2)	Explanation of the participation in social support groups	
3)	Interventionist checks and evaluates with the caregiver the strategies, material, and use of the handbook offered in previous sessions	
4)	Interventionist identifies and initiates a problem-solving approach focusing on the caregiver’s individual risk behaviour or problems	
5)	Interventionist provides training in different stress management techniques	
6)	Closure for each session:	
	a)	establishing date/time of next session
	b)	briefly reviewing problem areas
	c)	briefly reviewing strategies used
	d)	helping the caregiver implement strategies in daily routine
At the conclusion of the session, the interventionist completes a protocol of the session		

### Outcomes

Demographic information from the informal caregivers as well as from the people with dementia will be gathered via a questionnaire during the baseline assessment. In this trial, the outcome of primary interest is the effect on the burden of care-giving. Caregiver burden is perceived as a multi-dimensional response to stressors associated with care giving. We use a translated version of the Zarit Burden Inventory (ZBI [12]). The ZBI is a widely used 22-item assessment tool for measuring the caregiver’s perceived burden [13,14]. The data will be gathered at baseline, after intervention completion (six months), and at the follow-up nine months after baseline. Secondary outcomes are changes in the depression [15], somatisation [16], health-related quality of life [17] and social support of the family caregivers [18]. In addition, with regard to the relative with dementia, two further secondary outcomes will be collected: the effects on health-care service utilisation and problem behaviour [19] (see Table 2).

**Table 2 T2:** Measurements

**Point of measurement**	**Measures**
*Baseline assessment:*	
- caregiver sociodemographics	- sociodemographic data questionnaire
*Baseline assessment with regard to people with dementia:*	
- sociodemographic information	- sociodemographic data questionnaire
- degree of cognitive impairment	- SIDAM score
*Primary outcome:*	
- caregiver burden	- ZBI
*Secondary outcomes:*	
- depression	- PHQ-4
- somatisation	- PHQ-15
- health-related quality of life	- SF-12
- social support	- ESSI
*Secondary outcomes with regard to people with dementia:*	
- health-care service utilisation	- 1 question
- problem behaviour	- RMBC

**Note.** SIDAM = Structured Interview for Diagnosing Alzheimer-Type Dementia, Multi-Stroke Dementia, and Dementias of other Aetiology according to DSM-III-R and ICD-10); ZBI = Zarit Burden Inventory; PHQ-4 = Patient Health Questionnaire - 4 items; PHQ-15 = Patient Health Questionnaire -15 items; SF-12 = Short-Form Health Survey -12 items; ESSI = ENRICHD Social Support Inventory; RMBC = Revised Memory and Behaviour Checklist.

### Sample size calculation

The calculation of sample size was based on an updated meta-analysis determining the effectiveness of interventions for family caregivers of older adults [20]. In that study, a moderate mean effect size of 0.65 (95% CI [0.46-0.84,]) was determined for multi-component interventions on caregiver burden. Assuming this effect size as significant for DeREACH, which is a multi-component intervention, and using a t-test for two independent samples with a 0.05 two-sided significance level, a sample size of 51 patients per group was calculated to have 90% power for detecting a treatment effect of that size (calculated by G*Power [21]). Allowing for a drop-out rate of 35%, a total of 69 informal caregivers per group is planned.

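### At the stated 35% drop-out, 69 caregivers per group leave about 45 completers, not the 51 needed for 90% power; power is then about 86%

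*Protocol article*

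**What the plan says.** The Sample size calculation section of the protocol article takes "a moderate mean effect size of 0.65" from a meta-analysis of caregiver interventions. It bases the calculation on a comparison "using a t-test for two independent samples with a 0.05 two-sided significance level" and reports that "a sample size of 51 patients per group was calculated to have 90% power for detecting a treatment effect of that size". The next sentence adds the allowance for loss: "Allowing for a drop-out rate of 35%, a total of 69 informal caregivers per group is planned". The Methods paragraph of the Abstract carries this forward as the total: "A total of 138 informal caregivers at home are recruited", which is 2 × 69. The Randomisation section aims for equal groups: "To obtain the same number of subjects in the intervention and the control group, we use a randomisation in blocks". The article gives no formula for the drop-out step, no second drop-out rate and no other reason for 69.

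**The concern.** A drop-out rate is a share of the people randomised. If 35% of them are lost, 65% remain, so the number to randomise is the number needed divided by 0.65. The planned 69 is too small for that. It looks as if 35% of the evaluable number was added instead.

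At stake is whether the article's sample size justification is true as written. It joins four figures: 51 evaluable per group, 90% power, 35% drop-out and 69 randomised per group. If they cannot all hold, the trial has less power than stated under its own assumption about loss, and the wrong justification would pass into the results paper.

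**Working it through.** **Inputs, all from the protocol article.** Standardised effect d = 0.65, two-sided alpha 0.05, power 90%, two-sample t-test, 51 per group before drop-out, drop-out 35% and 69 per group planned (Sample size calculation); equal allocation (Randomisation); total 138 (Abstract, Methods).

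**Step 1: reproduce the base number.** Power comes from the noncentral t distribution with 2n − 2 degrees of freedom and noncentrality d × √(n/2). Solving for 90% power at d = 0.65 gives n = 50.72, so 51 per group, with power 90.2%. The stated 51 reproduces, so the discrepancy lies only in the drop-out step.

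**Step 2: the drop-out step, two ways.**

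| Rule | Calculation | Per group | Total |
|---|---|---|---|
| Divide by the share retained | 51/(1 − 0.35) = 78.46 | 79 | 158 |
| Add 35% of the evaluable number | 51 × 1.35 = 68.85 | 69 | 138 |

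Only the second rule gives the planned figure. Starting from the normal-approximation base of 50 does not explain 69 either: division gives 77 and multiplication gives 68.

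**Step 3: what 69 per group leaves.** 69 × (1 − 0.35) = 44.85, about 45 completers per group, which is 6 short of 51. This result does not depend on how 69 was reached.

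**Step 4: power at d = 0.65 with those completers.**

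| Completers per group | Power |
|---|---|
| 44 | 85.4% |
| 44.85 | 86.1% |
| 45 | 86.2% |
| 51 | 90.2% |

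If each caregiver drops out independently with probability 0.35, so that the number of completers varies, the average power is 85.8%.

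**Step 5: the effect detectable with 90% power.** At 44.85 per group it is d = 0.692, against the planning value of 0.65.

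**Step 6: the drop-out that 69 per group can absorb.** 1 − 51/69 = 0.261, so about 26%. Completers-only power across drop-out rates, with 69 randomised per group:

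| Drop-out | Completers per group | Power at d = 0.65 |
|---|---|---|
| 20% | 55.2 | 92.3% |
| 25% | 51.75 | 90.6% |
| 30% | 48.3 | 88.5% |
| 35% | 44.85 | 86.1% |

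**The case against.** **The loss is small.** At the plan's own drop-out rate it is about 4 points, and power stays above 80%. It is also small beside the uncertainty in the effect itself: over the confidence interval that the article gives for the effect (0.46 to 0.84), power with 51 per group runs from 63% to 99%. This stands. It limits how serious the point is, but it does not make the four figures agree.

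**The 35% may have meant a margin on top of 51.** The article prints no formula, so the 51 × 1.35 step is inferred, however close the match. But the text calls the 35% a drop-out rate. If a margin was meant, the drop-out actually covered is about 26%, and the sentence needs correcting on that reading too.

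**The primary analysis includes everyone randomised.** The Data analysis section plans an intention-to-treat t-test and names EM and multiple imputation, so a reader might infer that all 69 per group count in full. The article does not support that. It adds a drop-out allowance on top of 51, and so treats drop-out as lost information; imputing missing six-month scores does not in general restore all of that information. If all 69 counted in full, power would be 96.6% and no allowance would have been needed. What stands is that 86% is a completers-only figure and should be labelled so.

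**Baseline adjustment could restore the power.** A reader might infer that analysis of covariance makes up the shortfall. The Data analysis section uses it only if the groups differ significantly at baseline, and the article gives no correlation between baseline and six-month burden scores. Suppose that 0.65 is scaled to the standard deviation of the change score. Adjustment then multiplies the effective d by √(2/(1 + r)), where r is that correlation. With 44.85 per group, power is 94% at r = 0.5, 91% at r = 0.7, 89.4% at r = 0.8 and 87.8% at r = 0.9. Full recovery needs r of about 0.76 or less, so it cannot be claimed without an assumption about r.

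**Conclusion.** The figures in the Sample size calculation section are incompatible. The base of 51 per group is right, but 69 per group with 35% drop-out leaves about 45, and power for d = 0.65 is about 86%, some 4 points below the stated 90%. Keeping 51 at that drop-out would take 79 per group.

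The 86% rests on three conditions: a loss of 35% of primary outcome data in each group, a true effect of 0.65, and a t-test on completers.

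A reader might go further and infer that the trial runs a type II error about 40% larger than stated (14% against 10%). The document does not support that as a statement about the trial. It is true only under the three conditions above, the drop-out that will occur is not known from the article, and at 26% or less there is no shortfall at all. Expressed as a ratio, a 4-point difference also looks larger than it is.

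This is an error in the stated justification. It leaves the analysis and the type I error untouched, and it should be fixed.

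**What to change.** Keep 138 and replace the drop-out sentence with wording such as:

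> With 69 caregivers randomised per group, 35% drop-out leaves about 45 completers per group. A t-test on completers then has about 86% power for an effect size of 0.65, and 90% power for an effect size of 0.69. Power of 90% for an effect size of 0.65 holds only if drop-out is at most 26%.

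If any gain from baseline adjustment is to be mentioned, state the assumed correlation between baseline and six-month scores and show power over a range of values.

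The cost is one sentence and a slightly less favourable power statement. No participants are added and the analysis does not change. The alternative, if 90% power at 35% drop-out must be kept, is 79 per group: 158 in total, 20 more than planned. With recruitment already open since 1 October 2012 and only 4 points of power at issue, restating is the proportionate choice.

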### Data analysis

All analyses will be conducted using Statistical Packages for Social Sciences (SPSS) version 20.0 for Microsoft Windows. The change from baseline to post-intervention assessment (six months) on the ZBI (primary outcome) will be compared between treatment groups using t-tests for independent samples on all randomised informal caregivers (intention-to-treat population). In case of significant between-group differences at baseline, an analysis of the covariance will be used with the post-intervention score as a dependent variable and treatment group and baseline ZBI score will be used as additional covariates. Several SPSS methods with missing value imputation will be used, including expectation maximisation (EM) and multiple imputations. Secondary analyses of the primary outcome variable will be performed on informal caregivers treated per protocol (PP population). Secondary study outcomes will be subjected to an explorative analysis. Post-hoc analyses will be performed on the primary outcome variable in patient subgroups, defined for instance by age, sex, caregiver education, family relationship and cognitive ability of the care recipient at baseline. Secondary and post-hoc analyses will be explorative without multiplicity adjustment.

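### Baseline ZBI adjustment in the primary analysis depends on a baseline significance test; unconditional ANCOVA would give more power and one fixed primary result at no cost

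*Protocol article*

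**What the plan says.** The Data analysis section sets the primary comparison as ZBI change from baseline to six months, which "will be compared between treatment groups using t-tests for independent samples on all randomised informal caregivers (intention-to-treat population"). It then adds a switch: "In case of significant between-group differences at baseline, an analysis of the covariance will be used with the post-intervention score as a dependent variable", with treatment group and baseline ZBI as the other terms in the model. It does not state which baseline variable or variables are tested, or at what level.

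The Methods part of the Abstract gives the t-test alone: change "will be compared between treatment and control group using t-tests for independent samples". The Sample size calculation also rests on that test, "using a t-test for two independent samples with a 0.05 two-sided significance level". Nowhere does the article state a baseline-adjusted analysis of the primary outcome that is carried out whatever the baseline test shows.

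**The concern.** A baseline significance test in a randomised trial tests a null hypothesis that is true by design. Its result does not show whether an imbalance matters for the outcome. Here it nevertheless decides which model produces the trial's one confirmatory result.

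Three things are at stake:

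- **Power.** Almost all trials run under this rule would use the change score, which is noisier than ANCOVA whenever the baseline to six-month correlation is below 1.
- **Conditional bias.** A change score subtracts baseline with slope 1. With equal SDs at the two times the appropriate slope is the correlation, rho. A group that starts higher by chance will therefore seem to fall further, through regression to the mean.
- **A single fixed result.** The estimate and p-value depend on a preliminary test that the article does not define. If the test covers variables other than ZBI, the switch fires more often. The named model would still adjust only for baseline ZBI and not for the variable that fired.

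**Working it through.** **Inputs from the article.** Two-sided alpha 0.05; "a moderate mean effect size of 0.65"; "a sample size of 51 patients per group was calculated to have 90% power for detecting a treatment effect of that size"; "Allowing for a drop-out rate of 35%, a total of 69 informal caregivers per group is planned". Allocation is equal (Randomisation section: "To obtain the same number of subjects in the intervention and the control group, we use a randomisation in blocks").

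**Assumptions.** The documents do not give rho; 0.5 to 0.8 is used. SDs are taken as equal at the two times and the data as bivariate normal. The trigger is taken to be a 5% t-test on baseline ZBI. The article does not say whether 0.65 is in units of the SD of change or of the raw score, so both are shown.

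**1. The plan's own figure.** The noncentral-t calculation for d = 0.65 gives n = 50.7, so 51 per group, with power 0.902. The stated 51 is reproduced. With 69 randomised and 35% lost, 69 x 0.65 = 44.85, about 45 per group, where the t-test has power 0.862. This ignores any gain from the planned imputation.

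**2. Relative efficiency.** With score SD s:

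- Var(change) = 2(1 - rho)s²
- Var(ANCOVA residual) = (1 - rho²)s²
- Ratio = (1 - rho²) / [2(1 - rho)] = (1 + rho)/2

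This is 0.75, 0.80, 0.85 and 0.90 at rho 0.5, 0.6, 0.7 and 0.8.

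**3. Power of the two-stage rule, 0.65 in change-SD units** (simulation):

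| rho | 51/group: rule vs ANCOVA | 45/group: rule vs ANCOVA |
|---|---|---|
| 0.5 | 0.910 vs 0.961 | 0.872 vs 0.938 |
| 0.7 | 0.905 vs 0.938 | 0.868 vs 0.907 |
| 0.8 | 0.90 vs 0.93 | 0.86 vs 0.89 |

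The loss is about 2 to 7 points. It grows at lower rho: at rho 0.3 and 51 per group it is 0.913 vs 0.980. ANCOVA alone would need 39 per group (rho 0.5) or 44 (rho 0.7) for 90% power.

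**4. Power with 0.65 in raw-SD units.** The effect becomes 0.65/√[2(1 - rho)] for the change t-test and 0.65/√(1 - rho²) for ANCOVA. The two-stage rule stays close to the t-test because the switch is rare.

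| rho | 51/group: change t-test vs ANCOVA | 45/group: change t-test vs ANCOVA |
|---|---|---|
| 0.5 | 0.902 vs 0.964 | 0.862 vs 0.941 |
| 0.7 | 0.987 vs 0.995 | 0.976 vs 0.990 |
| 0.8 | 0.999 vs 1.000 | 0.998 vs 0.999 |

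Allowing for the rare switch, the rule loses about 5 to 7 points at rho 0.5 and about 1 point or less from rho 0.7.

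**5. Type I error.** The simulated two-stage rule gives about 0.040, 0.043 and 0.047 at rho 0.3, 0.5 and 0.7 with 51 per group. The arithmetic at rho 0.5 shows why. When the baseline test fires (5% of trials) the change t-test would reject 0.188 of the time under the null, and the switch replaces that with ANCOVA's 0.05: 0.0498 - 0.05 x 0.188 + 0.05 x 0.05 = 0.043.

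**6. Conditional bias.** Given a baseline difference D (in SDs), the change-score difference is displaced by (1 - rho) x D, in the opposite direction to D.

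- With 69 per group the significance boundary is about 1.96 x √(2/69) = 0.33 SD. There the bias is 0.3 x 0.33 = 0.10 SD at rho 0.7 and 0.5 x 0.33 = 0.17 SD at rho 0.5.
- The average absolute difference with 69 per group is 0.136 SD, giving 0.04 to 0.07 SD.
- A difference above 0.30 SD that does not fire the test occurs in about 3% of trials with 69 per group.
- With 51 per group, a difference above 0.2 SD without a switch occurs in about 26% of trials.

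**The case against.** The strongest defence is that a t-test on change is a legitimate analysis of a randomised trial. It matches the sample size calculation and reaches the stated 90% at 51 per group if 0.65 is in change-SD units. The loss exists only relative to a better method. This stands, and it is why the point concerns efficiency and pre-specification.

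A reader might infer more from the conditional clause, but the documents do not support four stronger readings:

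- **That non-significant imbalance is left uncorrected.** The outcome is change, so baseline is subtracted in full. The fault is over-correction.
- **That the two-stage rule inflates false positives.** On the reading simulated here it is slightly conservative.
- **That the pretest changes the estimand.** Under randomisation both models target the same mean difference in six-month ZBI. Only the estimate and p-value depend on the test, and the change-score estimate is unbiased over randomisations.
- **That bias of 15 to 25% of the planning effect is to be expected.** That is 0.10/0.65 to 0.17/0.65, a boundary case that also requires 0.65 to be in raw-SD units. At the average imbalance it is 0.04/0.65 to 0.07/0.65, roughly 6 to 10% on the same scale.

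It is also fair that the full protocol or analysis plan may define the trigger. The point does not depend on that gap: a conditional rule, however defined, remains inferior to adjusting always. A different trigger would change the 5% and 95% figures and the power values.

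**Conclusion.** The point holds as a should-fix. The stated rule yields a valid but less efficient primary analysis and makes the choice of model depend on an uninformative test. With rho assumed between 0.5 and 0.8, the loss against unconditional ANCOVA is about 2 to 7 power points if 0.65 refers to the SD of change. If it refers to the raw SD, the loss falls from about 5 to 7 points at rho 0.5 to about 1 point or less from rho 0.7. With about 45 completers per group and the change-SD reading, the rule has about 0.87 power, while ANCOVA is at or above 0.90 for rho up to 0.7. The direction of the result does not depend on rho, apart from one lost degree of freedom as rho approaches 1. Its size does, and the documents supply neither rho nor the scale of the effect.

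**What to change.** Amend the Data analysis section so that ANCOVA of six-month ZBI on treatment group and baseline ZBI is the single, unconditional primary analysis, reported as the adjusted difference with a 95% CI. Delete the baseline significance test and the conditional clause. Keep the change-score t-test as a sensitivity analysis, and bring the Abstract into line.

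The baseline ZBI is already collected on every participant and the model is already named, so no data, visits or participants are added. The sample size can stay: a calculation built on the t-test is conservative for ANCOVA on the same effect. The cost is a documented, dated amendment. Because recruitment began on 1 October 2012 and study staff are not blinded, it must be made before outcome data are examined; a later choice between the two models would not be credible.

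### The primary comparison is to be run with several unranked imputation methods, one of them EM, and a t-test on EM-filled scores is defective whether or not treatment arm is in the EM model

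*Protocol article*

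**What the plan says.** The Data analysis section compares the change in ZBI from baseline to six months between groups, "using t-tests for independent samples on all randomised informal caregivers (intention-to-treat population"). An ANCOVA replaces the t-test if the groups differ significantly at baseline. The next sentence, placed before the per-protocol and secondary analyses, deals with missing data: "Several SPSS methods with missing value imputation will be used, including expectation maximisation (EM) and multiple imputations". It does not say which method carries the primary test, whether the others are sensitivity analyses, or what happens if they disagree. Only the secondary and post-hoc analyses are declared explorative.

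The Sample size calculation section shows that substantial loss is expected: "Allowing for a drop-out rate of 35%, a total of 69 informal caregivers per group is planned".

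**The concern.** An analysis of all randomised caregivers, with up to about a third of the primary outcome missing, depends heavily on how the gaps are filled. EM used as an imputation tool normally returns one completed data set in which each missing score is replaced by its predicted value. An ordinary t-test on that data set counts 69 observed scores per group when only about 45 to 51 exist, and the filled values carry no residual scatter. Multiple imputation with pooled standard errors avoids both problems. The two methods can therefore give different p-values from the same data, and the plan has no rule for which one decides the trial. At stake are the error rate of the primary test, the width of its confidence interval and, in one version of the EM model, the size of the estimated effect.

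**Working it through.** **Inputs from the article.** Two-sided alpha 0.05, effect size 0.65, 90% power, 51 evaluable and 69 randomised per group, equal allocation, drop-out 35%.

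**Assumed, because the article does not give it.** The baseline to 6-month ZBI correlation ρ, varied from 0 to 0.9; complete baseline scores; 6-month scores missing completely at random and equally in both arms; one EM fill from baseline ZBI, with or without treatment arm.

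**The plan's own figures.** The exact two-sample t-test calculation gives n = 50.7, so 51 per group (power 90.2%), as stated. The 69 is 51 × 1.35 = 68.9. Two levels of loss therefore matter:
- a literal 35% loss leaves 69 × 0.65 = 44.9, about 45 per group (24 missing);
- keeping 51 of 69 means 18 missing, or 1 − 51/69 = 26%.

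**Arm in the EM model.** Let n = 69, let n_o be the number observed per group, and f = n_o/n. With unit variances, the large-sample variances of the difference in mean change are
- true: 2 × [(1−ρ)²/n + (1−ρ²)/n_o];
- reported by the t-test: 2 × [(1−ρ)² + (1−ρ²)f]/n.

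Their ratio is (reported SE/true SE)² = [(1−ρ) + (1+ρ)f] / [(1−ρ) + (1+ρ)/f]. The type I error is approximately 2 × [1 − Φ(1.96 × SE ratio)].

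Worked case, ρ = 0.6 and n_o = 45:
- true SE = √(2 × [0.16/69 + 0.64/45]) = 0.182;
- reported SE = √(2 × [0.16 + 0.64 × 0.652]/69) = 0.129;
- ratio 0.71, type I error about 16%.

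Simulation at 35% missing (69 per group, 24 missing per group, 8,000 null trials per setting) agrees with the formula:

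| ρ | SE ratio, formula | SE ratio, simulated | Type I, formula | Type I, simulated |
|---|---|---|---|---|
| 0 | 0.81 | 0.81 | 11% | 11% |
| 0.3 | 0.76 | 0.76 | 14% | 13% |
| 0.5 | 0.73 | 0.73 | 15% | 15% |
| 0.6 | 0.71 | 0.72 | 16% | 16% |
| 0.7 | 0.70 | 0.69 | 17% | 18% |
| 0.8 | 0.68 | 0.67 | 18% | 19% |
| 0.9 | 0.67 | 0.67 | 19% | 19% |

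Running EM separately by arm gives nearly the same results. The ANCOVA fallback on EM-filled data has a simulated SE ratio of 0.65 and a type I error of about 20%.

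At 26% missing (f = 51/69 = 0.739), the formula gives 9% at ρ = 0 and 13.5% at ρ = 0.8. Simulation gives 12% at ρ = 0.5 and 13% at ρ = 0.7.

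**Arm left out of the EM model.** The filled scores then carry no arm difference, so only the observed fraction contributes and the expected effect is f × 0.65. At 35% missing this is 0.652 × 0.65 = 0.42 (simulated 0.42 to 0.43), a loss of about 35%. At 26% missing it is 0.739 × 0.65 = 0.48. In simulation the SE ratio is about 1.0 and the type I error about 5%.

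**Comparators.** Multiple imputation with arm in the model (20 imputations, Rubin's rules) held the type I error at 4.4 to 5.3%. Observed cases only, 45 per group, gave 4.9%, with 86% power for an effect of 0.65. At 35% missing, ρ = 0.6 and arm in both models, EM was significant and multiple imputation was not in 11.5% of null trials.

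**The case against.** The strongest objection is that the inflated error rate depends on a modelling choice the article does not state. If arm is omitted from the EM model, the test keeps its level. A reader might infer a flat false-positive rate near 17%, over three times nominal, or that EM always gives the smaller standard error. The article supports neither. Those figures need arm in the EM model, a correlation of about 0.6 to 0.7 and a full 35% loss, and at 26% missing the rate is lower. This part of the objection stands, so the size is given here as a conditional range. It does not clear the plan, because the version without arm biases the effect towards zero.

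The wording also leaves room. The article does not call the EM fill single; that reading rests on the contrast with multiple imputations. EM might be meant only for stray missing items among the 22 of the ZBI, with multiple imputation for drop-out, and running several methods could be meant as sensitivity analysis. A reader might infer that the most favourable result will be picked afterwards, but nothing in the article says so. What remains is that the sentence rules out none of these uses and ranks nothing.

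Finally, this is a condensed article, and the analysis plan is not shown. The variables in the imputation model, the number of imputations and analyses for data not missing at random are commonly settled there, and their absence is no finding. The unranked list that includes EM is different, because the article itself commits to it.

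**Conclusion.** The point holds in conditional form. The article commits the intention-to-treat primary comparison to several imputation methods, EM among them, and gives none priority. One EM fill followed by an ordinary t-test is then defective in either version:
- **Arm in the EM model:** standard error about 19-33% too small and type I error about 11-19% at 35% missing (ρ from 0 to 0.9); type I error about 9-14% at 26% missing (ρ from 0 to 0.8).
- **Arm left out:** type I error near 5%, but the effect shrinks by about a third at 35% missing.

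These sizes rest on whole 6-month scores being filled once from baseline ZBI, on values missing completely at random with equal loss in both arms, and on an assumed correlation. That EM-filled data should not be analysed as if observed does not depend on the exact figures.

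**What to change.** Before data analysis, name one primary missing-data method with valid standard errors. Multiple imputation, which the article already lists, is enough: include treatment arm and baseline ZBI in the imputation model, apply the stated t-test to each completed data set, and pool by Rubin's rules. A likelihood-based mixed model without imputation is an alternative. Do not use EM-filled data for inference, and label any other method a sensitivity analysis that does not decide the trial. Curing the defect does not require changing the primary test.

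The cost is a few sentences of wording. The confidence interval will be wider than one from EM-filled data with arm in the model, and that is its correct width.
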